## Methods

### Study Design

We will use a single-subject alternating treatment approach with A1-B-A2-C-A3 or A1-C-A2-B-A3 design to study the effects of HIIT on motor and non-motor performance and neuroplasticity and neurodegeneration biomarkers such that subjects will perform both the HIIT (B-phase) and the moderate CAE training (C-phase) for 4 weeks. After a baseline (A1) period of 4 weeks, the first intervention period of 4 weeks will take place (B or C), followed by a washout period of 8 weeks without an intervention (A2), the second intervention period of 4 weeks (B or C), and finally a third washout period of 8 weeks (A3). Each patient therefore experiences the full set of treatment approaches. The order of interventions B and C will be randomized for each participant (i.e., ABACA or ACABA, two of each, four participants total) using a random sequence generator. Assessment will be done by Good Clinical Practice (GCP)-trained blinded assessors.

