## Abstract

**Background:** People with Parkinson's disease (PD) experience not only motor problems but also non-motor problems that seriously impede their daily functioning and quality of life. The current pharmacologic treatment of PD is symptomatic, and alternative rehabilitation treatments, which preferably also have a disease-modifying effect and promote neuroplasticity, are needed. Recent studies suggest that high-intensity interval training (HIIT) is promising for promoting neuroplasticity in human PD, with short training time and reduced burden. Biomarkers for neuroplasticity such as brain-derived neurotrophic factor (BDNF) and neurodegeneration (including neurofilament NfL and α-synuclein) may play a role, but their response to HIIT is not well-investigated.

**Objectives:** The aims of this study were (1) to study the effects of 4 weeks of HIIT compared with 4 weeks of continuous aerobic exercise on motor and non-motor outcomes of PD and (2) to investigate the association between HIIT, motor/non-motor performances changes, and blood biomarker levels for neuroplasticity and neurodegeneration.

**Study Design:** Single-subject research design with alternating treatment setup (ABACA) and frequent repeated measurements was used. Each participant received different intervention conditions (B/C) interspersed with baseline periods (A, i.e., ABACA or ACABA), and frequent repeated assessment of outcome measures is done to quantify within-subject, individual response patterns with sufficient power for data analysis. Blood samples were collected once a week in the baseline and training phases (A1 and B/C) and once every 2 weeks in the washout phases (A2 and A3).

**Intervention:** Four subjects with PD on stable dopaminergic medication, two in Hoehn–Yahr stage 1–2, and two in Hoehn–Yahr stage 2.5–3 followed an ABACA or ACABA schedule, consisting of blocks with 30-min sessions of “B” (HIIT) or 50-min sessions of “C” [continuous aerobic exercise (CAE)] 3×/week for 4 weeks, separated by baseline “A” periods of 8 weeks for a total duration of 28 weeks.

**Outcome Measures:** Outcome measures include disease status [Movement Disorder Society-sponsored revision of the Unified Parkinson's Disease Rating Scale (MDS-UPDRS)], blood biomarkers (BDNF, Nfl, and α-synuclein), measures for functional mobility (including an activity tracker), and activities of daily living, as well as cognition, mood, biorhythm (sleeping problems), and quality of life.

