### Study Population

This exploratory pilot study aims to recruit a convenience sample of four subjects with confirmed idiopathic PD on stable dopaminergic medication via the outpatient clinic for movement disorders at Amsterdam UMC, Vrije Universiteit Medical Center, Amsterdam, the Netherlands. Patients are asked in the study information letter to maintain a stable medication schedule throughout the study, unless the treating neurologist deems it medically necessary to adapt drug treatment. When applicable, this will be recorded and taken into account in the analysis. The study was approved by the Medical Ethics Committee of Amsterdam UMC, Vrije Universiteit Medical Center (nr. 2029.083). The study will be conducted in compliance with the Declaration of Helsinki.

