### Inclusion and Exclusion Criteria

Inclusion criteria are (1) diagnosis of idiopathic PD according to UK Brain Bank criteria (26); (2) Hoehn–Yahr stage 1 (*n* = 2 patients) and 2.5–3 (*n* = 2 patients) as confirmed by a trained assessor; (3) age between 55 and 80 years; (4) sufficient cognition to comprehend training instruction [Montreal Cognitive Assessment (MoCA) score > 21]; and (5) able to provide written informed consent. Exclusion criteria are (1) history of neurologic deficits other than PD; (2) severe fluctuating responses to dopaminergic medication; (3) psychiatric, musculoskeletal, or metabolic disorders prohibiting participation in intensive exercise training; (4) cardiovascular disorders or cardiac risk prohibiting participation in intensive exercise training as assessed by Lausanne Questionnaire [>2 risk items scored “yes”; Bille et al. (27)]; and (5) participation in a professionally supervised high-intensity therapy/exercise program to improve fitness in the 2 months before inclusion.

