### Training Protocol

Subjects will perform HIIT or moderate CAE on a stationary bicycle (Lode Corival, Lode Inc.) 3×/week for two periods of 4 weeks in a group of four subjects (Figure 1). The order of the intervention phases will be randomized. Training will take place on Mondays, Wednesdays, and Fridays, to allow for sufficient recovery periods between training sessions.

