### Statistical Analysis

Although the protocol specifies primary and secondary study outcomes, we will assess the results based on a combination of those parameters.

For example, the primary research parameter that we have specified is the MDS-UPDRS-III, which is measured before and after each phase. If, under the influence of the interventions, there are improvements within the participants that are greater than the measurement error of 3.25 points known from the literature (48), this is a clear indication that the intervention influences motor function. However, if there is less or no change in the MDS-UPDRS-III but in one or more other parameters, this is still informative with regard to the effects of the different interventions and the underlying mechanisms. If no change is visible in any parameter under the influence of the interventions in any participant (through visual analysis and/or statistical tests), then the conclusion should be that there is no effect.

Visual inspection is the method of choice for single-subject research designs (SSRDs) (24). We will inspect, analyze, and describe the changes across the baseline and intervention phases (phase mean level and data spread), and we will compare the trend (slope) of scores with the baseline mean levels and variability (standard deviations) on outcomes for each intervention strategy and each patient. Longitudinal regression analysis with “phase” (i.e., condition) as the independent variable will be used for further confirmation (α = 0.05).

We will not explicitly test for group differences between patients in Hoehn–Yahr stage 1–2 or for patients in Hoehn–Yahr stage 2.5–3, but we will get insights on the direction of effects and effect sizes in the intervention phases compared with the baseline phases, which we will report descriptively for both participants in both subgroups.

The association between biomarkers and symptom changes will be quantified by Pearson correlation coefficients and corrected for age, between changes in BDNF, α-synuclein, and Nfl and change scores on primary and secondary parameters.

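### The lower Hoehn–Yahr stratum is stage 1 in the inclusion criterion but stage 1–2 elsewhere, and training order is not stated to be randomised within the stage pairs (a one-in-three chance of order–stage confounding if it is not)

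*Protocol article*

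**What the plan says.** **Stage strata.**
- Inclusion and Exclusion Criteria: "Hoehn–Yahr stage 1 (*n* = 2 patients) and 2.5–3 (*n* = 2 patients) as confirmed by a trained assessor".
- Abstract (Intervention): "Four subjects with PD on stable dopaminergic medication, two in" Hoehn–Yahr stage 1–2 and two in stage 2.5–3.
- Statistical Analysis: the two subgroups are again stage 1–2 and stage 2.5–3.

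**Allocation.**
- Study Design: "The order of interventions B and C will be randomized for each participant (i.e., ABACA or ACABA, two of each, four participants total", drawn "using a random sequence generator".
- Training Protocol: "The order of the intervention phases will be randomized". Nothing is added about stage.

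**Use of the strata.** Statistical Analysis plans no formal test between the stage groups. It does expect insight into the direction and size of effects in the training phases against the baseline phases, "which we will report descriptively for both participants in both subgroups".

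**Timing.** Measurement Procedures and Training places baseline testing before allocation and lists Hoehn–Yahr stage among the baseline characteristics.

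**The concern.** There are two linked problems with the stage pairs.

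The first is who may be enrolled. The operative criterion and the analysis section give different ranges for the same stratum. A recruiter who follows the criterion turns away a stage 2 patient. A reader of the analysis section expects such a patient in the lower-stage subgroup. With two places per stratum, this governs half the sample.

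The second is how order is drawn. The sample is deliberately made of two stage pairs and results are to be described for each pair, yet the only stated restriction on the draw is two of each order across all four people. Under that rule, both lower-stage participants may train in one order and both higher-stage participants in the other. The by-stage descriptions would then mix treatment with period, and stage with order.

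The two training periods are not interchangeable, on the plan's own account:
- The Introduction describes the disease as progressive, and the study runs 4 + 4 + 8 + 4 + 8 = 28 weeks.
- The first training block follows 4 weeks of A1 with no study training before it. The second follows 8 weeks of A2 that come after a training block.
- In Table 1, blood sampling, TUG, 10-m walk and one-leg stance are weekly in A1 but every two weeks in A2.
- The Stroop test and Trail Making Test are repeated from phase to phase, so practice effects are possible.

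**Working it through.** **1. Stratum definitions side by side**

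| Place | Lower pair | Higher pair |
|---|---|---|
| Inclusion criterion | stage 1, n = 2 | stage 2.5–3, n = 2 |
| Abstract | stage 1–2, n = 2 | stage 2.5–3, n = 2 |
| Statistical Analysis | stage 1–2 | stage 2.5–3 |

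The higher pair agrees everywhere. The lower pair does not, and no passage resolves it. Places affected: 2 of 4.

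**2. The plan's own allocation figure**

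2 ABACA + 2 ACABA = 4 participants, which agrees with Study Population ("aims to recruit a convenience sample of four subjects with confirmed idiopathic PD"). The plan gives no probability of confounding, so there is no further figure to reproduce.

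**3. Chance that order lines up with stage, taking the stated restriction as the only one**

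Label the lower-stage participants E1 and E2 and the higher-stage participants L1 and L2. Choosing which two receive ABACA gives C(4,2) = 6 equally likely allocations:
- {E1, E2}: order and stage coincide
- {L1, L2}: order and stage coincide
- {E1, L1}, {E1, L2}, {E2, L1}, {E2, L2}: one of each order in each pair

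P(complete confounding) = 2/6 = 33.3%.

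Alternative rules:
- *Independent coin toss per person* (16 outcomes): complete confounding 2/16 = 12.5%, and all four on one order 2/16 = 12.5%. This rule does not guarantee two of each order, so it does not fit the text.
- *One of each order within each pair*: 2 × 2 = 4 allocations. All four give two of each order overall, and confounding is 0/4 = 0.

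**4. What a confounded draw does**

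Let d be the true HIIT minus CAE effect and p a shift from the first to the second training period. Assume the shift is additive and common to all four people.
- ABACA (HIIT first): observed HIIT − CAE = d − p
- ACABA (CAE first): observed HIIT − CAE = d + p

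Pair with one of each order: mean = [(d − p) + (d + p)]/2 = d.

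Pair with the same order: mean = d − p or d + p. No participant of the same stage has the opposite order, so d and p cannot be separated.

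Comparison of stages, with the lower pair on ABACA and the higher pair on ACABA: (d_L + p) − (d_E − p) = (d_L − d_E) + 2p. A stage difference cannot be told from an order effect.

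All four people, in any of the six allocations: [2(d − p) + 2(d + p)]/4 = d. The overall contrast is balanced over period whichever allocation is drawn.

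**The case against.** The strongest objection is that the document never says stage is ignored. Drawing one of each order within each pair would also yield two of each over four participants, so the quoted sentence is compatible with the proposed remedy, and a journal article may leave such detail to the full protocol. This stands. A reader might infer that order is definitely not randomised within the pairs; the text is silent, and the 33% is conditional on two-of-each being the only restriction.

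The next objection concerns harm. This is an exploratory pilot in which each person is examined singly, every participant receives both kinds of training, an A phase lies before and after each block, and 8 weeks of A2 separate them. These features reduce drift and carry-over, though they do not remove them. A reader might infer that the main HIIT–CAE comparison is compromised. It is not, because order is balanced 2:2 in every allocation and no between-stage test is planned.

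A reader might also infer that in a same-order pair the HIIT–CAE difference is nothing but a period difference. That goes too far: it is treatment effect plus period shift, and the two are inseparable.

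It can further be said that the by-stage output compares training with baseline phases, not HIIT with CAE. That is so, but it gives limited relief. In a confounded draw, one pair's HIIT block always follows A1 and the other pair's always follows A2, so these effect sizes also rest on different reference phases.

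Finally, the remedy leaves one person per order in each stage, so within a pair order is tied to the individual. This stands too; the gain is real but modest.

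None of these objections touches the mismatch in the stage range, where the stated ranges simply disagree.

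**Conclusion.** Both parts hold, with different strength.

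The stratum mismatch is a plain contradiction in the text: stage 1 in the criterion, stage 1–2 in the Abstract and the analysis section. It concerns two of four places and must be reconciled. The documents do not show which range is intended.

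The allocation point is conditional. Order is not stated to be randomised within the stage pairs. If two of each order over four is the sole restriction, the chance of complete order–stage confounding is 2/6 = 33%. The consequence is confined to the descriptive by-stage reporting. The overall HIIT–CAE contrast remains balanced over period, and a period shift common to all four participants cancels from it. The result assumes equally likely allocations and an additive, common shift; the size of that shift cannot be had from the document.

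This should be corrected, chiefly for the eligibility contradiction and secondarily for an avoidable risk to a planned output.

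**What to change.** 1. Use one Hoehn–Yahr range for the lower pair in the inclusion criterion, the Abstract and Statistical Analysis. This costs a one-line correction.
2. State that order is randomised 1:1 within each Hoehn–Yahr pair, one ABACA and one ACABA per pair. If this is already the practice, one clause settles it. It needs no extra participant, visit or analysis: stage is recorded before allocation, and two of each order overall is still met. The chance of order–stage confounding falls from 33% to 0. The article does not say whether all four are enrolled before the draw, but this is not required, because an order list can be prepared in advance for each stage. With staggered enrolment, the second member's order follows from the first's, so the lists should be kept from those who recruit.
3. Keep the by-stage results descriptive, and say that within each stage every order rests on a single person.

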### Study Population

This exploratory pilot study aims to recruit a convenience sample of four subjects with confirmed idiopathic PD on stable dopaminergic medication via the outpatient clinic for movement disorders at Amsterdam UMC, Vrije Universiteit Medical Center, Amsterdam, the Netherlands. Patients are asked in the study information letter to maintain a stable medication schedule throughout the study, unless the treating neurologist deems it medically necessary to adapt drug treatment. When applicable, this will be recorded and taken into account in the analysis. The study was approved by the Medical Ethics Committee of Amsterdam UMC, Vrije Universiteit Medical Center (nr. 2029.083). The study will be conducted in compliance with the Declaration of Helsinki.

### Inclusion and Exclusion Criteria

Inclusion criteria are (1) diagnosis of idiopathic PD according to UK Brain Bank criteria (26); (2) Hoehn–Yahr stage 1 (*n* = 2 patients) and 2.5–3 (*n* = 2 patients) as confirmed by a trained assessor; (3) age between 55 and 80 years; (4) sufficient cognition to comprehend training instruction [Montreal Cognitive Assessment (MoCA) score > 21]; and (5) able to provide written informed consent. Exclusion criteria are (1) history of neurologic deficits other than PD; (2) severe fluctuating responses to dopaminergic medication; (3) psychiatric, musculoskeletal, or metabolic disorders prohibiting participation in intensive exercise training; (4) cardiovascular disorders or cardiac risk prohibiting participation in intensive exercise training as assessed by Lausanne Questionnaire [>2 risk items scored “yes”; Bille et al. (27)]; and (5) participation in a professionally supervised high-intensity therapy/exercise program to improve fitness in the 2 months before inclusion.

### Measurement Procedures and Training

All testing and training will be performed in the “on” state, ~1–1.5 h after medication intake. Prior to allocation, subjects will complete baseline testing for demographics and for motor and non-motor symptoms (Table 1). Assessment of demographics and baseline characteristics will include, age, height, weight, sex, disease duration, Movement Disorder Society-sponsored revision of the Unified Parkinson's Disease Rating Scale (MDS-UPDRS I to IV), Hoehn–Yahr stage and LEDD (levodopa equivalent daily dose), medication schedule and usage (dopaminergic, psychopharmacological, and any other medications), and number of falls in past month.

Table 1Assessment schedule for outcomes across the 28-week study period.

**Table d38e472:** 

**Schedule**																									
	**Phase**	**Baseline A1**												**Intervention B/C**											
	**Week**	**1**			**2**			**3**			**4**			**1**			**2**			**3**			**4**		
	**Session**	**s1**	**s2**	**s3**	**s1**	**s2**	**s3**	**s1**	**s2**	**s3**	**s1**	**s2**	**s3**	**s1**	**s2**	**s3**	**s1**	**s2**	**s3**	**s1**	**s2**	**s3**	**s1**	**s2**	**s3**
Tests	Cardiac Screening	x																							
	Demographics	x																							
	VO_2_ test												x												
Motor	UPDRSI-IV	x												x											
	TUG	x			x			x			x			x											
	10m walk	x			x			x			x			x			x			x			x		
	one-leg-stance	x			x			x			x			x			x			x			x		
Cognition	MoCa	x																							
	Stroop test	x												x											
	TMT	x												x											
	PD-CFRS	x												x											
	VAS-concentration	x			x			x			x			x	x	x	x	x	x	x	x	x	x	x	x
Mood	BDI	x												x											
	VAS-mood	x			x			x			x			x	x	x	x	x	x	x	x	x	x	x	x
Sleep	Scopa sleep	x												x											
	VAS-sleep	x			x			x			x			x	x	x	x	x	x	x	x	x	x	x	x
ADL	NEAI	x												x											
QoL	PDQ-8	x												x											
Blood	BDNF/NfL, α-syn	x			x			x			x			x			x			x			x

**Table d38e1278:** 

	**Phase**	**Baseline A2**																								**Intervention C/B**											
	**Week**	**1**			**2**			**3**			**4**			**5**			**6**			**7**			**8**			**1**			**2**			**3**			**4**		
	**Session**	**s1**	**s2**	**s3**	**s1**	**s2**	**s3**	**s1**	**s2**	**s3**	**s1**	**s2**	**s3**	**s1**	**s2**	**s3**	**s1**	**s2**	**s3**	**s1**	**s2**	**s3**	**s1**	**s2**	**s3**	**s1**	**s2**	**s3**	**s1**	**s2**	**s3**	**s1**	**s2**	**s3**	**s1**	**s2**	**s3**
Tests	Cardiac Screening																																				
	Demographics																																				
	VO_2_ test																								x												
Motor	UPDRSI-IV	x																								x											
	TUG	x						x						x						x						x											
	10m walk	x						x						x						x						x			x			x			x		
	one-leg-stance	x						x						x						x						x			x			x			x		
Cognition	MoCa																									x											
	Stroop test	x																								x											
	TMT	x																								x											
	PD-CFRS	x																								x											
	VAS-concentration	x			x			x			x			x			x			x			x			x	x	x	x	x	x	x	x	x	x	x	x
Mood	BDI	x																								x											
	VAS-mood	x			x			x			x			x			x			x			x			x	x	x	x	x	x	x	x	x	x	x	x
Sleep	Scopa Sleep	x																								x											
	VAS-sleep	x			x			x			x			x			x			x			x			x	x	x	x	x	x	x	x	x	x	x	x
ADL	NEAI	x												x												x											
QoL	PDQ-8	x												x												x											
Blood	BDNF/NfL, α-syn	x						x						x						x						x			x			x			x

**Table d38e2389:** 

	**Phase**	**Baseline A3**																																			
	**Week**	**1**			**2**			**3**			**4**			**5**			**6**			**7**			**8**		
	**Session**	**s1**	**s2**	**s3**	**s1**	**s2**	**s3**	**s1**	**s2**	**s3**	**s1**	**s2**	**s3**	**s1**	**s2**	**s3**	**s1**	**s2**	**s3**	**s1**	**s2**	**s3**	**s1**	**s2**	**s3**
Tests	Cardiac Screening																								
	Demographics																								
	VO_2_ test																								
Motor	UPDRSI-IV	x																							x
	TUG	x						x						x						x					x
	10m walk	x						x						x						x					x
	one-leg-stance	x						x						x						x					x
Cognition	MoCa																								x
	Stroop test	x																							x
	TMT	x																							x
	PD-CFRS	x																							x
	VAS-concentration	x			x			x			x			x			x			x					x
Mood	BDI	x																							x
	VAS-mood	x			x			x			x			x			x			x					x
Sleep	Scopa Sleep	x																							x
	VAS-sleep	x			x			x			x			x			x			x					x
ADL	NEAI	x												x											x
QoL	PDQ-8	x												x											x
Blood	BDNF/NfL, α-syn	x						x						x						x					x

*Planning of baseline (A1, A2, and A3), intervention (B and C), and measurements (crosses indicate time movements). Pre–post phase measurements will be performed before and after both baseline and both intervention phases*.

*UPDRS, MDS-Unified Parkinson's Disease Rating Scale; MoCa, Montreal Cognitive Assessment; PD-CFRS, PD Cognitive Functioning Rating Scale; Stroop, Stroop test; VAS, visual analog scale; BDI, Beck Depression Inventory; ADL, activities of daily living; Scopa Sleep, Sleep scale from Scopa; NEAI, Nottingham Extended ADL index; QoL, quality of Life; PDQ-8, Parkinson's Disease Questionnaire; BDNF, brain-derived neurotrophic factor; NfL, neurofilament light; α-syn, alpha synuclein*.

